### Ethical approval

The study protocol complied with the ethical standards described in the Declaration of Helsinki. All methods of this study will be performed in accordance with the relevant guidelines and regulations. The Ethics Committee of Guangdong Provincial Hospital of Chinese Medicine has approved the study protocol for this trial (Approval number: ZF2023-040-01), and it has been registered on the Chinese Clinical Trial Registry (Trial registration number: ChiCTR2300072292. Registered on June 08, 2023). Each participant will have sufficient time to decide whether to participate in the trial or not and written informed consent must be obtained before randomization. Cetirizine Hydrochloride tablets will be provided if AR attacks interfere with participants' quality of life. Participants will be required to document relief medication use in their diaries. Any alterations or modifications to the study protocol must be communicated to the Ethics Committee of Guangdong Provincial Hospital of Chinese Medicine, Guangzhou, China, and reported to the Chinese Clinical Trials Registry. Written informed consent will be obtained from the patients and be aware of the potential benefits and risks.

## Discussion

In China, a multicenter study found that the majority of AR patients have persistent symptoms with or without seasonal aggravation [37]. Previous trials evaluating the effect of acupressure on AR did not differentiate between SAR and PAR. Considering of the characteristics of AR, only PAR patients clinically diagnosed with symptoms lasting for at least 6 months per year will be enrolled in this trial.

Intranasal corticosteroids are considered the first-line pharmacological treatment for AR due to their safety, fast action, and ability to alleviate symptoms, decrease mucus membrane permeability, and improve quality of life [1, 38]. Two long-term studies [39, 40] evaluating the safety of mometasone furoate nasal spray in children or adolescents with AR yielded positive results. Therefore, mometasone furoate nasal spray will be used as the routine treatment in this trial.

Acupuncture, a long-standing non-pharmacological treatment for AR, has been recommended as an effective alternative for symptom alleviation, improved quality of life, and reduced medication side effects [41], with supporting evidence from numerous randomized clinical trials.

Mechanisms of acupuncture for AR have also been extensively studied. Lei RL and colleagues [19] demonstrated that acupuncture exhibits anti-inflammatory and antihistaminic effects by effects by downregulating proinflammatory cytokines and neuropeptides. A recent review [42] summarized that acupuncture modulates anti-inflammatory actions in AR through various pathways, including upregulating Th1 cytokines, downregulating Th2 and proinflammatory cytokines, and affecting proinflammatory neuropeptides and neurotrophies. Clinical studies on AR patients have suggested that acupuncture treatment improves the balance between T-helper 1 (Th1) and T-helper 2 (Th2) cell-derived pro-inflammatory versus anti-inflammatory cytokines, as evidenced by differential gene expression in peripheral blood before and after acupuncture therapy [26].

Acupressure, a noninvasive and alternative form of treatment, involves applying pressure to acupoints on the body. Acupoints correspond to different organs and systems in the body [43]. Acupressure is more precise than massage, which targets broader areas to soften tissues. These advantages may align more closely with patient preferences, potentially improving adherence. Several studies have indicated that acupressure can effectively alleviate AR symptoms such as sneezing, itching, rhinorrhea, and nasal obstruction, while also enhancing quality of life [15]. In addition to its ease of use, acupressure avoids the skin irritation associated with herbal patch therapy by stimulating specific acupoints through mechanical pressure, without the use of medications.

How dose acupressure affect AR? The pathogenesis of AR in the nasal mucosa involves a complex network of inflammatory responses, encompassing various cells, mediators, cytokines, chemokines, and neuropeptides [3, 8, 9]. These phenomena are governed by cellular and molecular mechanisms that include the delicate balance between innate immune mechanisms and Th1-Th2 imbalance. Th1 T-cells primarily release IFN-γ, which plays a role in delayed hypersensitivity immune reactions [44]. TSLP, an epithelial-derived cytokine similar to IL-17, is known to induce deregulation of Th2 responses and increase the expression of chemokines that attract Th2 cells, a hallmark feature of allergic inflammatory diseases such as AR and asthma [45]. Th2 cells contribute to IgE synthesis and affect accessory cells like eosinophils, basophils, and mast cells. IL-5, an important Th2 cytokine associated with AR, can upregulate the expression of adhesion molecules, facilitating the recruitment of inflammatory cells into nasal and bronchial tissues [46]. IL-13, another key Th2 cytokine related to AR, is linked to decreased epithelial barrier integrity mediated by activated Th2 cells and may influence mucosal barrier permeability [47]. Nasal secretions, comprising cells, plasma exudation, and mucus from goblet cells and seromucous glands, will be collected bilaterally from each participant upon enrollment in the trial. The trial will observe, record, and compare the changes in the levels of IL-5, IL-13, TSLP, and IFN-γ in the nasal secretions to explore their variations.

To the best of our knowledge, this is the first clinical trial of comparing self-administered specific acupoint acupressure group and a blank control group. Additionally, it is the first trial to monitor the process online. Blinding of researchers and participants is not possible due to the nature of acupressure; however, participants will be blinded during the entire randomization process. Although non-specific acupoints have not been reported for the treatment of AR, investigation is needed to determine the therapeutic effects of acupressure on these non-specific acupoints in this trial. This trial also represents the first attempt to explore the mechanism of acupressure for PAR by analyzing and comparing cytokines in nasal secretions. It is expected to contribute valuable knowledge to fill the gaps in research. Compared to previous studies on acupressure for PAR, this trial features several innovations and advancements, including clearer diagnostic criteria for PAR classification and a more rigorous methodology. To ensure a well-designed trial, the following aspects were considered: random allocation to prevent selection bias and assessment of trial outcomes using both clinician-administered and self-reported measures.

There are certain limitations in this trial. First of all, a sham acupoint control group will not be established due to difficulties in defining sham acupoints. Secondly, individual differences in the sensitivity of acupoints and the applied pressure strength are not uniform, warranting a larger sample size to identify patterns in acupressure for AR. In this protocol, we have described a three-arm, randomized, controlled trial to examine the safety and efficacy of ARAT in treating PAR. This study will provide reliable information on the therapeutic effects of ARAT and help elucidate its potential immunologic mechanism.

In conclusion, this trial offers a standardized and practical protocol to guide current and future research. Furthermore, it contributes to the accumulation of clinical experience regarding acupressure on specific acupoints. By investigating the effectiveness and safety of acupressure, the findings of this trial are expected to provide positive evidence in support of its use for PAR patients. Moreover, the results will offer valuable insights for healthcare professionals in managing PAR symptoms.

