**Methods/design:**

In this trial, eligible 111 participants diagnosed with PAR will be randomly assigned to one of three groups: the ARAT group, the non-specific acupoints group, or the blank control group. The primary outcome will be the change in the total nasal symptom score, and the secondary outcomes will include: 1) changes in the scores of the standard version of Rhinoconjunctivitis Quality of Life Questionnaire (RQLQs); 2) acoustic rhinometry and anterior rhinomanometry; 3) changes in the scores of relief medication usage; 4) incidence of adverse events. Additionally, we will measure and compare the changes in cytokine levels (IL-5, IL-13, IFN-γ, and TSLP) in nasal secretions.

The RQLQs and primary outcomes will be assessed at the beginning, middle, and end stages of the treatment period, with monthly follow-ups conducted over a total of three months. The secondary outcomes and biomarkers in nasal secretions will be measured at the beginning and end of the treatment period. Any adverse events or need for rescue medication will be carefully noted and recorded.

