### Sample size

The primary outcome measure is Total Nasal Symptom Score (TNSS). As there are no existing studies on ARAT, a new type of acupressure, the sample size calculation was based on a pilot study of ARAT for PAR that utilized the same outcome measure (Table 2). Using these results and considering the study's objectives, the sample sizes for the ARAT group and the non-specific acupoints group were separately calculated for comparison with the blank control group. The calculations were performed with α=0.05 and β=0.1, and the maximum sample size for each group was determined to be 33 cases using PASS11.0 (NCSS, LLC. Kaysville, UT, USA) software. Accounting for a potential 10% dropout rate, a total sample size of 111 participants will be recruited for this trial, with 37 participants allocated to each group.

**Table 2 Tab2:** Pilot study of ARAT for perennial allergic rhinitis

	**the ARAT group**	**the non-specific acupoints group**	**the blank control group**

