Additionally, the treatment mechanism of ARAT will be explored in this trial. Nasal secretions from eligible participants will be collected by research nurses at the beginning and end of the treatment. These biological specimens will be centrifuged and stored in the Biological Resource Center of SCCGZUCM for molecular analysis. Cytokines such as interleukin-5 (IL5), IL13, thymic stromal lymphopoietin (TSLP), and interferon-gamma (IFN-γ) will be detected using the enzyme-linked immunosorbent assay (ELISA) method.

Among these outcome measures, TNSS and RQLQs will be assessed at the beginning, middle, and end of treatment period, as well as during the follow-up period at weeks 4, 8, and 12. The other measures will be assessed at the beginning and end of the treatment period.

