### Statistical analysis

Qualified statisticians who are blinded to the treatment group data will perform all efficacy and safety analyses following the intention-to-treat (ITT) principle using SPSS 20.0 (IBM SPSS Inc., Armonk, New York, USA). Missing values will be estimated using the last recorded data. A significance level of α= 0.05 will be considered statistically significant. The median, minimum, and maximum values will be used to express measured data. Group comparisons will be analyzed using Analysis of Variance (ANOVA) and pairwise comparisons (rank-sum test for univariate variance). Count data will be expressed as composition ratios or rates, and comparisons between groups will use the χ2 test for efficiency and rank-sum test for efficiency and rank-sum test for ranked data.

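### The only stated cytokine analysis compares changes in level by ANOVA and rank-sum tests; if levels are skewed and effects proportional, this can lose substantial power against a log-scale, baseline-adjusted model

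*Protocol article*

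**What the plan says.** The abstract (Methods/design) announces that "we will measure and compare the changes in cytokine levels (IL-5, IL-13, IFN-γ, and TSLP) in nasal secretions", and the mechanism paragraph of the Discussion repeats the aim in nearly the same terms, to "compare the changes in the levels of IL-5, IL-13, TSLP, and IFN-γ in the nasal secretions". Under Secondary outcome measures, "Nasal secretions from eligible participants will be collected by research nurses at the beginning and end of the treatment", so each participant should have a paired baseline and end value.

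The Statistical analysis section does not mention cytokines by name. It gives a general rule: "Group comparisons will be analyzed using Analysis of Variance (ANOVA) and pairwise comparisons (rank-sum test for univariate variance"), with "The median, minimum, and maximum values will be used to express measured data" and "A significance level of α= 0.05 will be considered statistically significant". It names no transformation, ratio or baseline covariate, and it excludes none.

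The Sample size section concerns TNSS only: "The calculations were performed with α=0.05 and β=0.1". The Discussion expects the trial to "help elucidate its potential immunologic mechanism".

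**The concern.** ELISA concentrations are positive. They are often right-skewed, and a treatment often shifts them by a proportion; both are assumptions here. If they hold, the absolute change is the participant's own baseline multiplied by a proportional change, so spread in baseline level enters the treatment comparison as noise.

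The design can make this worse. All three arms receive the same mometasone nasal spray during the intervention period, and the samples bracket that period. A fall common to all arms is therefore plausible. It would shrink the absolute between-arm difference while the baseline-driven noise stays.

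The cytokines are the trial's only mechanistic evidence, and the trial was not sized for them. A real proportional effect could give a non-significant result and be read as no immunologic action, although the same samples might have shown it.

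**Working it through.** **1. The plan's own figure.** No power or sample size is stated for the cytokines. The recruitment figure reproduces from 33 per group and 10% dropout: 33 / 0.9 = 36.7, rounded up to 37; 3 × 37 = 111.

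**2. Inputs.** From the article: 37 per arm, two sampling times, α = 0.05 (taken as two-sided). Assumed, because the article gives nothing: log-normal levels, natural-log SD σ from 0.3 to 1.2, correlation ρ = 0.5 between log baseline and log end value, and control-arm levels at end of treatment equal to c = 1.0, 0.8 or 0.6 times baseline.

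**3. Effect size.** The ARAT/control ratio is set so that log-scale ANCOVA has about 90% power in a pairwise comparison: δ = 3.29 × σ × √(1 − ρ²) × √(2/37), ratio = exp(−δ). For σ = 0.8: 3.29 × 0.8 × 0.866 × 0.2325 = 0.530, and exp(−0.530) = 0.59. For σ = 0.3, 0.5 and 1.2 the ratios are 0.82, 0.72 and 0.45.

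**4. Power by simulation** (4,000 trials per setting, Monte Carlo standard error at most 0.8 points). Entries are for σ = 0.3 / 0.5 / 0.8 / 1.2.

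| Analysis | Controls stable (c = 1.0) | c = 0.8 | c = 0.6 |
|---|---|---|---|
| t test, absolute change | 73 / 65 / 50 / 33% | 60 / 52 / 37 / 25% | 39 / 35 / 25 / 18% |
| Rank-sum, absolute change | 73 / 68 / 63 / 56% | 61 / 57 / 52 / 49% | 40 / 40 / 38 / 39% |
| Rank-sum, end level only | 77–79% | 78–79% | 77–78% |
| t test, log(end/beginning) | 80–81% | 80–81% | 79–80% |
| ANCOVA, log end on log beginning | 89–90% | 89–91% | 89–90% |

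Repeat runs move entries by one or two points. Over those runs absolute change spans about 31–73% (t test) and 56–74% (rank-sum) with stable controls, and about 18–41% and 37–42% at c = 0.6.

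**5. Separating the two changes.** Moving from absolute change to log ratio isolates the scale and brings power to about 80%. Adding log baseline as a covariate contributes about 10 points more.

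**6. Why each test loses.** In the ANOVA or t test a few high values dominate. The three most extreme of 37 carry a median 41%, 47%, 59% and 73% of the within-arm sum of squares of absolute change at σ = 0.3, 0.5, 0.8 and 1.2. The rank-sum test bounds each participant's weight, so its loss has another source. Absolute change equals X(r − 1), with X the baseline and r the participant's end/beginning ratio. Ranks of X(r − 1) mix baseline level with effect, most of all when nearly everyone falls.

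**7. Type I error.** With no effect, rejection was between 4% and 6% for every method in every setting.

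**8. Sensitivity.** A wider grid used 33 per arm, σ 0.5–1.2, correlation 0.5–0.85, ratio 0.5 or 0.7, and c = 1.0, 0.7 or 0.5. Log ANCOVA had at least 80% power while absolute change had below 50% in 22 of 72 settings for ANOVA and 13 of 72 for rank-sum. With stable controls the counts were 2 of 24 and 0 of 24; with controls halving, 12 of 24 and 10 of 24. With σ = 0.5, correlation 0.7, a halving and stable controls, every method had about 100%. With σ = 1.2, correlation 0.5, ratio 0.7 and stable controls, power was about 10% (ANOVA), 20% (rank-sum) and 30% (log ANCOVA), so the log scale usually missed the effect too.

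**The case against.** **The text does not fix end minus beginning.** This stands. A log ratio is also a change in level, the mechanism sentence is narrative, and the statistical section rules out no transformation. Absolute change is the natural reading, but it is a reading.

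**The Outcomes section also speaks of comparing groups at the end of treatment.** If that covers the cytokines, a rank-sum test on end levels gives the same result on the raw and log scales and has about 77–79% power. This removes most of the scale problem. It still leaves about 11–13 points against log ANCOVA, because the collected baseline goes unused.

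**The scale of an exploratory biomarker belongs in an analysis plan that is not shown.** This is fair for an omission, and handling of undetectable values would not be a point by itself. But the article does state a variable and a test, and the question is whether that stated pair serves the data.

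**The size depends on invented inputs.** This stands. The control-arm fall is the main driver and its size is unknown. The simulations also model only falls, while the Discussion reports upregulated Th1 cytokines under acupuncture, and IFN-γ is a Th1 cytokine.

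A reader might infer that a real effect would usually be missed and that the log scale would show it, or that a few high secretors would dominate whichever test is used. The documents do not support this. They contain no cytokine distribution, correlation or effect; the grid above has settings where both scales succeed and where both fail; and dominance by a few values concerns the ANOVA only.

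**Conclusion.** The point holds in a conditional form. As published, the cytokine comparison is of changes in level by ANOVA and rank-sum tests, on no named scale and without baseline adjustment. If levels are right-skewed and effects proportional, a log-scale model with log baseline has more power on each reading of the text that was tried. Where it has 90%, the shortfall runs from about 11–13 points (rank-sum on end levels) to about 70 points (t test on absolute change, high skew, all arms falling to 60%).

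These figures rest on the assumed log-normal form, correlation 0.5, log SD 0.3–1.2 and the assumed control-arm course. Validity under the null is not in question and TNSS is untouched. The trial calls itself exploratory, and the cytokines are an additional look at mechanism. The change is worth making because it is cheap and this is the only mechanistic evidence.

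**What to change.** Add to the Statistical analysis section: each cytokine is log-transformed; arms are compared at the end of treatment by a linear model on log concentration with log beginning-of-treatment concentration as covariate; results are given as ratios of geometric means between arms with 95% CI; values below the assay limit follow one rule fixed before database lock, for example treatment as left-censored. Align the phrases about changes in cytokine levels in the abstract and Discussion with this.

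The cost is one or two sentences of analysis text, with no new sample, visit or participant. The small downsides are that effects are read as ratios instead of concentration differences, and that undetectable values need the stated rule.

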## Trial status

Recruitment began on July 1, 2023, and is anticipated to end on April 30, 2024.

## Data Availability

Following the completion of the present research, the datasets used and/or analyzed will be made accessible to the corresponding author upon reasonable request.

## Abbreviations

AcRh: Acoustic rhinometry
AEs: Adverse events
ANOVA: Analysis of Variance
AnRh: Anterior rhinomanometry
AR: Allergic rhinitis
CONSORT: Consolidated Standards of Reporting Trials
CRF: case report forms
ELISA: Enzyme-linked immunosorbent assay
IFN-γ: Interferon -gamma
IgE: Immunoglobulin E
IL5: Interleukin-5
ILC2s: Type 2 innate lymphocytes
ITT: Intention-to-treat
RCT: Randomized, controlled trial
RMs: Relief medication scores
RQLQs: Rhinoconjunctivitis Quality of Life Questionnaire score
SCCGZUCM: The Second Clinical College of Guangzhou University of Chinese Medicin
SPIRIT: Standard Protocol Items: Recommendations for Interventional Trials
STRICTA: Revised Standards for Reporting Interventions in Clinical Trials of Acupuncture
Th2: T helper 2
TIDieR: Intervention Description and Replication
TNSS: Total nasal symptom score
TSLP: Thymic stromal lymphopoietin
WHO: World Health Organization
